## **13 Evaluation criteria, methods, and interpretation of validity (based on statistical methods)**

### **13.1 Primary efficacy measures: wound size and degree of re-epithelialization**

- Wound size and degree of re-epithelialization in the control and experimental groups at 0 and 4 weeks were plotted against time, respectively, and differences between the two groups were analyzed using a paired t-test.
- Wound size and degree of re-epithelialization will be measured by the investigator on the day of the study visit by physically examining the pressure ulcer size (width × length × depth: measured in cm using a ruler). Photographs of the treated area will be taken, including a 1 cm X 1 cm grid at the time of measurement.

\*How to take clinical photographs: At the time of each visit, photographs should be taken at a 90° angle and at a distance of 15 cm, using the camera in use in the clinic. For consistent evaluation, ensure that the photographs are taken under the

same conditions (angle, same camera, etc.).

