| Clinical trial design       | Single-center, randomized, parallel design, prospective exploratory clinical trial                                                                                                                                                                                                                                                                                                                                                                                                                                                                                                                                                                                                                                                        |
| Number of subjects          | 38 participants (19 experimental, 19 control, 15% dropout rate)                                                                                                                                                                                                                                                                                                                                                                                                                                                                                                                                                                                                                                                                           |
| Clinical Trial Purpose      | For patients with mild pressure ulcer co-morbidity, the medical light irradiator 'BELLALUX Lite' was used as the Exploratory evaluation of safety and efficacy for wound repair                                                                                                                                                                                                                                                                                                                                                                                                                                                                                                                                                           |

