### **7.3 Number of subjects and rationale**

#### **7.3.1 Number of subjects**

Aim for **16 subjects per** endpoint **arm**, and account for a 15% dropout rate.  

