**38** subjects, **19 per control and experimental group, for a total of 38 subjects.**

#### **7.3.2 Rationale**

This study is an **exploratory trial** and is intended to provide a **basis for statistical validation of a confirmatory trial**. A systematic review of the effectiveness of photobiological therapy in the treatment of pressure ulcers by Francislene FCP et al. published in 2020 found that the five reviewed trials each had between 6 and 40 patients per arm, with an average of 15.8 patients per arm. We selected 16 subjects per arm as the minimum standard for this trial, with a predicted dropout rate of 15%. We will **target 19 subjects per group for the final evaluation**.

The dropout rate was **selected based on the fact that out** of 250 patients treated by a single professor ([name], Department of Plastic Surgery) over a **recent 2-year period**, 45 patients died within the study period, resulting in a mortality rate of **18%**. As the mortality rate is relatively high in patients with moderate and severe pressure ulcers, **we predicted that the mortality rate would be lower in the subjects included in this study and** set a dropout rate of 15%.

[figure not shown]

**Figure 12. Block** diagram of this study

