### **9.2.3 Randomization**

Subjects who meet the inclusion and exclusion criteria and agree to participate in the study will be assigned a subject identification code once they are finally selected. The order in which subjects are assigned to the treatment and control groups according to the subject identification number will be determined by the block randomization method using the statistical program "R" to assign randomization numbers of sufficient size, taking into account the predetermined block size. Once the randomization table is created, it is independently managed by a third party independent randomization manager.

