**13.2 Secondary validity measure: immunochemical markers on tissue examination**

- Pro-inflammatory cytokine (IL-6) / Anti-inflammatory cytokine (IL-10) ratio was obtained and the progression to the proliferative phase was analyzed by comparing the control and experimental groups after 0 and 4 weeks.
- Immunochemical markers are measured in a laboratory by a researcher through RNA sequencing, with final confirmation by the Principal Investigator.

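### The primary wound-size test fixed in Protocol 13.1 has no baseline covariate, although week-0 size is measured and neither entry nor randomisation controls it

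*Protocol*

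**What the plan says.** Protocol 13.1 describes the primary analysis so: "Wound size and degree of re-epithelialization in the control and experimental groups at 0 and 4 weeks were plotted against time". The same sentence then assigns the contrast between the arms to a paired t-test. The Analysis Methods row of the Protocol Summary names the same test. Neither place mentions a covariate or a model.

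Size is width × length × depth in cm, measured by the investigator at the visit (13.1).

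The sections that could restrict or balance starting size do not do so:
- Section 7.1 asks only for a stage 2 ulcer in the hip area and age 13 or over. No exclusion in 7.2 concerns ulcer size.
- Section 9.2.3 says the allocation order is "determined by the block randomization method". It states no stratification.

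On numbers, 7.3.1 says "Aim for 16 subjects per endpoint arm, and account for a 15% dropout rate", and the Protocol Summary gives "38 participants (19 experimental, 19 control, 15% dropout rate". Section 7.3.2 explains that 16 reflects the size of earlier trials: "the five reviewed trials each had between 6 and 40 patients per arm, with an average of 15.8 patients per arm". No alpha, power, effect size, standard deviation or correlation is given. Section 12.3 keeps dropouts in the analysis by last observation carried forward unless there is reason to exclude them.

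For the cytokine ratio, 13.2 speaks only of "comparing the control and experimental groups after 0 and 4 weeks" and names no test.

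**The concern.** In a small two-arm trial with the same quantity measured before and after treatment, the baseline value is the obvious covariate. Here ulcers of any size can enter, so starting size may vary a good deal. A larger ulcer also has more volume to lose, so an unadjusted change mixes starting size with device effect.

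The point is distinct from the choice of t-test. A paired test does not compare two independent arms, and that has to be corrected anyway. But replacing it with a two-sample t-test would leave the baseline issue where it is. Week-4 values alone discard baseline. Change scores subtract it with a slope fixed at 1, which over-corrects whenever the true slope is smaller.

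At stake is the precision of the estimate and its interval. Section 7.3.2 says the trial is meant to supply the statistical basis for a confirmatory trial, so the interval is a main product. No power calculation stands behind 16 per arm, so precision that costs nothing is worth having.

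**Working it through.** **The plan's own figure.** Section 7.3.2: "We selected 16 subjects per arm as the minimum standard for this trial, with a predicted dropout rate of 15"%. 16 / (1 − 0.15) = 18.8, rounded up to 19 per arm and 38 in total. This reproduces. There is no stated power to reproduce.

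**Inputs.** From the protocol: n = 16 evaluable per arm, 1:1 allocation. Assumed, because the protocol is silent: two-sided alpha 0.05, equal SD at both times, approximate normality, and a week-0 to week-4 correlation ρ of 0.3, 0.5 or 0.7.

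**Residual variance, in units of the outcome variance.**
- Week-4 values alone: 1
- Change from week 0: 2(1 − ρ)
- Week-4 values adjusted for week 0: 1 − ρ²

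The adjusted-to-unadjusted ratio is therefore 1 − ρ² against week-4 values, and (1 − ρ²) / [2(1 − ρ)] = (1 + ρ)/2 against change.

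**Power.** Noncentral t with noncentrality d × √(n/2), on 30 degrees of freedom unadjusted and 29 adjusted. The d that gives 80% unadjusted power at 16 per arm is 1.024, in SD units of the comparator. Under adjustment d is divided by the square root of the variance ratio.

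| ρ | Ratio vs week 4 | Adjusted power | Ratio vs change | Adjusted power |
|---|---|---|---|---|
| 0.3 | 0.91 | 83.5% | 0.65 | 93.4% |
| 0.5 | 0.75 | 89.8% | 0.75 | 89.8% |
| 0.7 | 0.51 | 97.5% | 0.85 | 85.9% |

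At ρ = 0.5 adjustment moves 60% to 72.3% and 50% to 61.8%. Allowing for estimation of the covariate slope lowers the results by 1 to 2 points at most (88.8% in place of 89.8%).

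**Sensitivity to the effect size.** At ρ = 0.5, the gain over week-4 values is 2.7 points for d = 0.3, 7.4 for 0.5, 12.3 for 0.8, 10.3 for 1.0 and 5.9 for 1.2. Across d = 0.3 to 1.2 and ρ = 0.2 to 0.8, with d in week-4 SD units, it runs from 0.3 to about 41 points over week-4 values and from about 0 to 22 over change scores.

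**Chance imbalance.** The standard error of the baseline mean difference is √(2/n) SD.
- 16 per arm: √(2/16) = 0.354; 0.5/0.354 = 1.414; the two-sided probability of a gap above 0.5 SD is 15.7%.
- 19 per arm, if all are kept under 12.3: √(2/19) = 0.324; 0.5/0.324 = 1.541; 12.3%.

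**The case against.** **The power figures are not the protocol's.** This stands. A reader might take from the ρ = 0.5 row that the plan forfeits about ten points of power. The documents do not support that as a fact: they state no power to lose, and from 80% the gain over week-4 values runs from about 3.5 to 17.5 points for ρ of 0.3 to 0.7, and wider if the effect size also varies.

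**Pairing already uses baseline.** This stands in part. If within-patient changes are compared between arms, baseline is subtracted rather than ignored. With the effect fixed at 1.02 week-4 SDs and ρ = 0.7, change scores already have 95.0% power and adjustment adds only 2.4 points. Starting instead from 80% change-score power, the gain at ρ = 0.7 is 6 points, and it grows as ρ falls. Subtraction is not adjustment: a chance baseline difference still enters the estimate whenever the true slope is not 1.

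**Chance imbalance is not bias.** Correct. Under randomisation the unadjusted estimate is unbiased on average, and a valid between-arm interval already carries this variability.

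**An analysis plan not shown could add the covariate.** Not for wound size: the protocol names its test in two places, so a different primary analysis elsewhere would contradict it. For the cytokine ratio the objection succeeds. A reader might infer from 13.2 that the ratio is to be compared unadjusted, but no test is named there. Adjustment is unspecified, not excluded. Biopsy is also limited to those who consent (10.2), so 16 per arm is not established for that endpoint.

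**Wound size may not suit a linear model.** This stands and shapes the fix. Size is a three-way product, and section 8 gives mild ulcers 1 to 3 months to heal, so skew and some zeros at week 4 are plausible.

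**Conclusion.** The point holds for the primary wound-size analysis. The protocol fixes a t-test with no covariate, although baseline is measured and neither the entry criteria nor the stated randomisation restrains it. The consequence is lost precision, and conditional imbalance in the single trial that will be run.

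The size of the gain depends on a correlation and an effect size that the protocol does not give. It is modest against week-4 values when the correlation is low, and modest against change scores when it is high. The analysis has not yet settled which of the two it uses. That baseline size predicts week-4 size well is a reasonable expectation, not something that the documents show.

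The finding does not extend to the cytokine ratio. Nor does it mean that the trial would give a biased answer or is invalid for want of adjustment. It is an inexpensive improvement that should be made while the paired t-test is being corrected.

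**What to change.** In the Analysis Methods row of the Protocol Summary and in 13.1, replace the paired t-test with a between-arm analysis of covariance: week-4 wound size on treatment arm, with week-0 wound size as covariate. Report the adjusted difference and its 95% confidence interval.

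Because some wounds may have closed by week 4, specify a transformed scale that accepts zero values, or add a rank-based sensitivity analysis.

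Analyse re-epithelialization, the other named primary measure, by the same between-arm model, with its week-0 value or week-0 wound size as covariate.

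The cost is rewording in two places and one residual degree of freedom. No visit, measurement or subject is added, and the same change removes the paired-test error.

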| Research Methods           | 
For subjects who signed the informed consent form of their own volition, after conducting the necessary examinations and tests according to the protocol, reviewing the inclusion and exclusion criteria, and deeming them suitable for this study, educating them about the study schedule and methods. Subjects will be irradiated with 4 different wavelengths of LEDs at maximum power (5 levels (<math>90\text{ mW}/\text{cm}^2</math> ) for a maximum duration (25 minutes) at a distance of 15 cm from the pressure ulcer in the buttock area. LED irradiation will be performed 3 times per week, with one week of treatment completed.
 
This is followed by a medical examination and wound assessment. This is done for a total of 4 weeks.
 |
| Evaluation Variables       | 
(1) Validation
 
 
1) Primary efficacy measures: wound size and degree of re-epithelialization
 
2) Secondary validity measure: immunochemical markers on tissue examination
 
 
(2) Assessing safety
 
 
1) Anomalies
 
2) Physical exam and vital signs
 
                                                                                                                                                                                                                                                                                                                                                                                             |
| Analysis Methods           | 
- Wound size and degree of re-epithelialization: calculate the wound size and degree of re-epithelialization of the control and experimental groups at 0 and 4 weeks, respectively, against time, and analyze the differences between the two groups using a paired t-test.
 
- Immunochemical markers on tissue examination: pro-inflammatory cytokine (IL-1, 6)/anti-inflammatory cytokine (IL-4, 10, 13) ratio at 0 and 4 weeks.
 
Analyzes progression to the proliferation phase by comparing control and experimental groups
                                                                                                                                                                                                                |

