### **9.2.2 Setting up a test/control group**

**Patients were randomized** into two groups, one with the investigational device and the other with a sham device. The purpose of the study is to prove the superiority of the device in treating pressure ulcers.

This medical device product is a class 2 medical combination stimulator, which is a light emitting diode (LED) device that combines a low power light irradiator (output light with an energy density of 20J/cm^2 or less than 2W/cm^2) and an infrared irradiator. The irradiation part is approximately 336 × 354 × 105 mm in size, and is designed to be easily applied to the desired location by adjusting the angle and direction at the head connection part, and the height of the product at the body part.

This is a prospective, exploratory, double-blind, randomized, parallel-group, prospective study with a control device (Sham device), which is identical in appearance to the study device and will be applied to control patients. The irradiated area of the control device is made to look similar to the irradiated area of the test device using LEDs of 12 mW/cm^2 or less. Patients are randomly assigned to either the test or control device with a 50% chance of being assigned to the test device upon consent.

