### **10.3 Observational Test Method**

**10.3.1 Screening Visit (Visit 1, -D14 to D1):** Subjects selected to participate in this study will receive an explanation of the study and be assessed in the following order.

Explain the test process and obtain written consent from subjects before allowing them to participate in the test.

Subjects are corrected on their screening numbers in order.

- ③ Investigate the subject's demographics and medical history.
- ④ For women of childbearing age, perform a pregnancy test.

Perform a physical exam and vital signs.

- ⑥ Measurement of erythema, Braden scale, and NRS.
- ⑦ Blood tests, urinalysis, and pelvic X-ray.

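### The primary analysis names a paired t-test for the difference between two independent randomised arms, where no pairs across arms exist

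*Protocol*

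**What the plan says.** Section 13.1 takes wound size and degree of re-epithelialization at 0 and 4 weeks in the control and experimental groups and states that "differences between the two groups were analyzed using a paired t-test". The Analysis Methods row of the Protocol Summary gives the same instruction: "analyze the differences between the two groups using a paired t-test". The protocol names no other test for the primary measures.

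The design is described elsewhere as follows:

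- The Protocol Summary calls the study a "Single-center, randomized, parallel design, prospective exploratory clinical trial".
- Section 9.2.2 randomises patients "into two groups, one with the investigational device and the other with a sham device", each "with a 50% chance of being assigned to the test device upon consent". It gives the purpose as showing superiority of the device.
- Section 9.2.3 has the allocation order "determined by the block randomization method using the statistical program" R. It mentions no matching.
- Nothing in the protocol describes a crossover, a within-patient control or matched pairs.

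**The concern.** A paired t-test needs a natural partner for every observation. Here the only natural pairs are the week-0 and week-4 values of the same patient, and those pairs lie within an arm. A difference between arms compares different patients, and no device patient has a sham partner.

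A statistician who follows the text literally has two options. One is to test the change within each arm, which does not address the randomised question. The other is to invent pairs across arms, which makes the p-value arbitrary. Section 7.3.2 says the trial is to provide a basis for a confirmatory trial. That needs a between-arm difference and a valid measure of its uncertainty, and the named test does not supply both on either reading.

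**Working it through.** **Inputs from the protocol.** Sections 7.3.1 and 7.3.2 plan 16 evaluable subjects per arm with 15% dropout, and randomise 19 per arm, 38 in total. This reproduces: 16 / 0.85 = 18.8, rounded up to 19, and 2 × 19 = 38. The 16 is taken from the average arm size (15.8) of five reviewed trials. No alpha, power, effect size or SD is stated, so the sample size does not rest on the choice of test.

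**Assumptions added here.** Two-sided alpha 0.05, normal data, independent arms. Effects are in SD units because the protocol gives no SD.

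**Reading (a): week 0 against week 4 within each arm.** Let both arms change by the same mean h, in SDs of the change score, so that there is no device effect. With n = 16, the power p of each within-arm test comes from the noncentral t with 15 df, critical value 2.131 and noncentrality h√16 = 4h. The arms are independent, so the chance that the device arm is significant and the sham arm is not is p(1 − p).

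| Common change h (SD) | p | p(1 − p) |
|---|---|---|
| 0.3 | 0.203 | 0.162 |
| 0.5 | 0.465 | 0.249 |
| 0.8 | 0.848 | 0.129 |
| 1.0 | 0.962 | 0.037 |
| 1.2 | 0.994 | 0.006 |

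A valid two-sided 5% test would falsely favour the device in 2.5% of trials. The product p(1 − p) cannot exceed 0.25, so the value at 0.5 SD sits almost at the ceiling. The rate falls quickly once both arms heal strongly, and at 1.2 SD it is below 2.5%.

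**Reading (b): pairing across arms.** With 16 per arm, the mean of the paired differences equals the difference of the arm means, whichever pairs are chosen. What changes is the following.

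- Degrees of freedom: an independent two-sample test has 2 × 16 − 2 = 30 (critical t 2.04). A paired test has 16 − 1 = 15 (critical t 2.13).
- Power at a true difference of 1 SD: the noncentrality is 1 × √(16/2) = 2.83 in both cases. Power is 78% for the independent test and 75% for the paired one. At 0.8 SD it is 59% and 56%.
- Dependence on the pairing: 300 data sets were simulated at 0.8 SD, with 200 random pairings each. The verdict at 0.05 changed with the pairing in about 45% of data sets. The median 5th and 95th percentiles of the p-value across pairings were 0.008 and 0.068.
- Unequal arms: if only completers were used and each of 19 per arm dropped out independently with probability 0.15, the numbers of completers would match in about 18% of trials, from Σ [C(19,k) 0.85^k 0.15^(19−k)]² over k = 0 to 19. Otherwise some patients have no partner.

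**The case against.** Several points on the other side have force.

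- **Translation.** The English text is visibly machine-translated, and the two statements of the test are nearly the same sentence, so the repetition is weak evidence of intent. A mistranslated test name is possible but cannot be shown from the document. The text still needs correcting.
- **A separate SAP may exist.** That would excuse missing detail. Here the protocol itself fixes the test, and a SAP naming a different one would contradict it.
- **No within-arm p-value contrast is prescribed.** This is correct. The rates under reading (a) describe what would follow if the within-arm results were set against each other. A reader might infer that false device claims are always far above 5%. The table does not support that: the rate is 3.7% at 1.0 SD and 0.6% at 1.2 SD.
- **The device effect might still be estimated.** A reader might infer that the stated analysis cannot estimate it at all. That is true of reading (a). Under reading (b) with equal arms, the point estimate is the ordinary between-arm difference, and the standard error, degrees of freedom and p-value are what fail. Section 12.3 retains dropouts by LOCF, which could keep the arms at 19 each, but it does not create pairs.
- **Baseline.** A reader might take week 0 to be the D0 screening visit, since section 10.3.1 heads it "Screening Visit (Visit 1, -D14 to D1". The protocol never says so. The tissue markers are also compared at 0 and 4 weeks, and section 10.2 takes those biopsies at D1, immediately before treatment. D29 is 28 days after D1. The protocol's own usage therefore points to D1.

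**Conclusion.** The primary analysis is wrong as written: it applies a paired test to independent arms, and the protocol supplies neither pairs nor another test for the primary measures. It should be corrected before any analysis.

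The damage depends on how the text would be read. Under within-arm tests with contrasted p-values, the false pattern in favour of the device ranges from about 25% to under 1%, depending on a common change that the protocol does not let us estimate. Under arbitrary cross-arm pairing, the loss of power is small (75% against 78% at 1 SD), and the real defect is a p-value that depends on who is paired with whom. That the test does not fit the design rests on none of these numerical assumptions.

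**What to change.** In the Analysis Methods row of the Protocol Summary and in section 13.1, replace the paired t-test with an independent-groups comparison for each of the two primary measures: wound size as section 13.1 defines it (width × length × depth) and degree of re-epithelialization.

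The preferred form is ANCOVA of the week-4 (D29) value on randomised arm, adjusted for the pre-irradiation D1 value where one is measured. Otherwise use a two-sample comparison of change. Report the between-arm difference with its 95% CI, and label any within-arm paired test as descriptive. State that week 0 means the D1 pre-irradiation assessment, so that the baseline is not left to inference.

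The cost is a wording change in two places. The sample size stays at 38 because it was not derived from a power calculation, and no visits or data are added.
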